## Abstract

**Background:**

The addition of antiplatelet therapy to anticoagulant therapy in patients with stroke with non-valvular atrial fibrillation (NVAF) and atherothrombotic disease may increase bleeding risk without reducing recurrent stroke risk.

**Aims:**

To evaluate the clinical benefits of anticoagulant monotherapy compared to combination therapy with anticoagulants and antiplatelet agents.

**Methods and design:**

This is an investigator-initiated prospective multicenter, randomized, open-label, parallel-group clinical trial. Patients with NVAF and atherothrombotic disease who have had a recent ischemic stroke or transient ischemic attack will be eligible to participate in this trial.

**Study outcomes:**

The primary outcome is a composite of ischemic cardiovascular events, including cardiovascular death, ischemic stroke, myocardial infarction, systemic embolism, ischemic events requiring urgent revascularization, and major bleeding events within 2 years after randomization.

**Sample size estimates:**

This study will enroll 400 patients, 200 receiving anticoagulant monotherapy and 200 receiving combination therapy. This sample size will provide 90% power (one-sided *p* = 0.025) to detect a risk reduction in outcome events within 2 years, assuming event rates of 13 and 27% for each group, respectively, and a 10% loss to follow-up at a 2.5% significance level with one-sided log-rank tests at an interim analysis and a final analysis.

**Discussion:**

This will be the first study to assess the net clinical benefit of oral anticoagulant monotherapy in ischemic stroke patients with NVAF and atherothrombosis.

**Clinical trial registration:**

https://clinicaltrials.gov/study/NCT03062319, NCT03062319; https://center6.umin.ac.jp/cgi-open-bin/ctr/ctr_view.cgi?recptno=R000029222, UMIN000025392; https://jrct.niph.go.jp/latest-detail/jRCTs051180202, jRCTs051180202.

## Introduction

1

Non-valvular atrial fibrillation (NVAF) and atherothrombotic disease frequently coexist, particularly in aging populations with shared risk factors such as hypertension and diabetes mellitus (1). Patients with both NVAF and atherothrombotic disease have an elevated risk of ischemic events, including stroke and myocardial infarction, as well as bleeding complications due to antithrombotic therapy. The current guidelines recommend oral anticoagulant therapy (OAC) for the prevention of stroke in patients with non-valvular atrial fibrillation (NVAF) (2, 3) and antiplatelet therapy for patients with non-cardiogenic stroke including large artery atherosclerosis and small vessel disease (4, 5). However, the optimal antithrombotic management for patients with both conditions remains uncertain due to limited evidence.

The combination of OAC and antiplatelet agents is often considered to reduce the risk of recurrent ischemic events (6, 7). However, recent studies have raised concerns regarding the safety and efficacy of this approach. The addition of antiplatelet agents to OAC has been associated with an increased risk of major bleeding (8). The AFIRE trial demonstrated that rivaroxaban monotherapy was non-inferior to combination therapy in terms of efficacy while significantly reducing bleeding risks in patients with NVAF and stable coronary artery disease (9). More recently, the EPIC-CAD trial also demonstrated that edoxaban monotherapy had higher clinical benefit than combination therapy in patients with NVAF and stable coronary artery disease (10). Meta-analyses provide further support for these findings, indicating that combination therapy may not provide a net clinical benefit over anticoagulant monotherapy (11). According to these results, the recent guidelines emphasize the importance of individualized antithrombotic therapy in patients with NVAF and atherothrombotic disease (12).

Furthermore, patients with a history of stroke or transient ischemic attack (TIA) who are receiving antiplatelet therapy are at an even higher risk of major bleeding when treated with OAC (8). Observational studies have demonstrated that the concomitant use of antiplatelet agents with OAC increases the composite outcome of cardiovascular and bleeding events without reducing recurrent stroke in patients with NVAF (13, 14). However, these findings are derived from non-randomized studies, and randomized controlled trials are required to establish the clinical benefit of OAC monotherapy in this context.

The optimal Antithrombotic Therapy in Ischemic Stroke patients with Non-Valvular Atrial Fibrillation and atherothrombosis (ATIS-NVAF) trial is designed to address this evidence gap. This investigator-initiated, prospective, multicenter, randomized control trial aims to evaluate the clinical benefits of OAC monotherapy compared to combination therapy with OAC and antiplatelet agents in patients who have experienced a recent ischemic stroke or TIA and have both NVAF and atherothrombotic disease. The results of this study could have significant implications for clinical practice, potentially informing guideline recommendations and optimizing antithrombotic therapy to improve patient outcomes.

## Methods

2

### Design

2.1

This is a protocol for an investigator-initiated, multicenter, prospective, randomized, open-label, parallel-group phase IV study.

### Patient population

2.2

This trial will be conducted at 41 sites in Japan. The inclusion and exclusion criteria for study enrollment are listed in Table 1. Eligible patients will be identified by their physicians during routine consultations. Figure 1 shows the flowchart of the study design.

**Table 1 tab1:** Eligibility criteria.

Inclusion criteria:
Acute ischemic stroke or TIA 8–360 days after symptom onset.
Age: ≥20 years
Patients with non-valvular atrial fibrillation (chronic or paroxysmal) who started or continued taking oral anticoagulants.
Patients with one of the following atherothrombotic diseases:
History of ischemic heart disease (myocardial infarction, angina pectoris, coronary artery bypass graft, or PCI).
History of peripheral artery disease (symptomatic peripheral arterial occlusive disease, lower-extremity bypass surgery/angioplasty/stenting).
Carotid artery stenosis (symptomatic or asymptomatic, ≥50% diameter), a history of carotid artery stenting or carotid endarterectomy.
Intracranial artery stenosis (≥50% stenosis of the diameter of a major intracranial artery: intracranial internal carotid artery, anterior cerebral artery A1 and A2, middle cerebral artery M1 and M2, posterior cerebral artery P1 and P2, vertebral artery, and basilar artery; a history of intracranial stent placement or intracranial bypass surgery).
History of ischemic stroke due to large-artery atherosclerosis or small-vessel occlusion.
Patients with modified Rankin Scale score ≤ 4.
Patients who can take oral medications.
Patients who can complete a follow-up survey.
Provision of written informed consent either directly or by a suitable surrogate.
Exclusion criteria:
History of myocardial infarction or acute coronary syndrome within the past 12 months.
Patients who underwent PCI with drug-eluting stents within the past 12 months or PCI with bare-metal stents within the past 3 months.
Patients who underwent carotid artery, intracranial, or lower-extremity stent placement within the past 3 months.
History of symptomatic intracranial hemorrhage or gastrointestinal bleeding within the past 6 months.
Hemorrhagic diathesis or blood coagulation disorders.
Platelet counts <100,000/mm^3^ at enrollment.
Severe anemia (hemoglobin <7 g/dL)
Severe renal failure (e.g., creatinine clearance ≤15 mL/min) or chronic hemodialysis.
Severe liver dysfunction (Grade B or C of the Child-Pugh classification).
Pregnant women
Active cancer
Expectation of survival <2 years
Anticoagulants or antiplatelets scheduled to be discontinued for >4 weeks during the follow-up period.
Planned revascularization procedure during the follow-up period.
Patients enrolled in other trials.
Patients judged as inappropriate for this study by the investigators.

PCI, Percutaneous coronary intervention; TIA, Transient ischemic attack.

**Figure 1 fig1:**
[figure not shown]
Study design flowchart. OAC, Oral anticoagulant therapy; TIA, Transient ischemic attack.

### Randomization

2.3

All patients who consent to participate and fulfill the eligibility criteria will be randomized to either the OAC monotherapy group or the combination therapy group with a 1:1 allocation according to a computer-generated randomization schedule using the Pocock-Simon minimization method, with adjustment for sex, history of ischemic heart disease, and history of acute ischemic stroke.

The participants will be randomized using the cloud-based electronic data capture service DDworks 21 (Fujitsu Ltd., Tokyo, Japan), an online central randomization service. Allocation concealment will be ensured because the service will not release the randomization code until the patient has been recruited into the trial, which takes place after all baseline measurements have been completed. Clinical events will be assessed by a blinded Independent Central Review Committee. Additionally, all other individuals involved in the study will be blinded to the treatment allocation.

### Intervention

2.4

Patients will receive either OAC monotherapy or OAC plus antiplatelet therapy at the discretion of the treating physician, in accordance with the protocols outlined in Table 2. The dose of each drug is consistent with the approved dose in Japan. Details of the drugs to be used in both groups are shown in Table 2. Treatment will start within 3 days after randomization and continue for 2 years. If the treating physician needs to change the OAC or antiplatelet drug during the study, the choice of drug may be changed based on the predefined drugs for each group (Table 2). Temporary interruption of study treatment is allowed during invasive procedures such as surgery but cannot exceed 4 weeks. Patients in both treatment groups will be treated according to the relevant guidelines for the prevention of stroke or systemic embolism.

**Table 2 tab2:** Allowed anticoagulant and antiplatelet drugs.

Anticoagulants
Select one of the following drugs:
Warfarin
Target INR of 2.0–3.0 if <70 years
Target INR of 1.6–2.6 if ≥70 years
Dabigatran
Full dose: 150 mg BID
Reduced dose: 110 mg BID if CCr <50 mL/min OR age ≥ 70 years OR history of gastrointestinal bleeding OR concomitant P-glycoprotein inhibitors
Rivaroxaban
Full dose: 15 mg OD
Reduced dose: 10 mg OD if CCr <50 mL/min
Apixaban
Full dose: 5 mg BID
Reduced dose: 2.5 mg BID if 2 of 3: age ≥ 80 years OR body weight ≤ 60 kg OR SCr ≥1.5 mg/dL
Edoxaban
Full dose: 60 mg OD
Reduced dose: 30 mg OD if body weight ≤ 60 kg OR CCr <50 mL/min OR concomitant P-glycoprotein inhibitors.
Antiplatelets
Select one of the following drugs:
Aspirin: 75–200 mg OD
Clopidogrel: 50 or 75 mg OD
Prasugrel: 3.75 mg OD
Ticlopidine: 100 mg BID OR 200 mg OD
Cilostazol: 50 or 100 mg BID

BID, Twice daily; CCr, Creatinine clearance; INR, International normalized ratio; OD, Once daily; SCr, Serum creatinine.

### Study outcomes

2.5

Follow-up visits will be scheduled at 6 ± 2, 12 ± 2, 18 ± 2, and 24 ± 2 months. Each follow-up visit will be conducted by the treating physician. Blood pressure measurements and laboratory examinations will be performed. Patients will be asked about any outcomes or adverse events that occurred before the follow-up visit.

The primary outcome is a composite of ischemic cardiovascular events, including cardiovascular death, ischemic stroke, myocardial infarction, systemic embolism, ischemic events requiring urgent revascularization, and significant bleeding, as defined by the International Society of Thrombosis and Hemostasis (ISTH) criteria (15) within 2 years after randomization.

Secondary outcomes include incidences of the following events within 2 years after randomization: (1) all-cause mortality; (2) ischemic cardiovascular events (cardiovascular death, ischemic stroke, myocardial infarction, systemic embolism, and ischemic events requiring urgent revascularization); (3) all ischemic cardiovascular events (ischemic cardiovascular events, TIA, unstable angina pectoris, and progression of symptomatic peripheral artery disease); and (4) ischemic stroke; and (5) myocardial infarction and cardiovascular death.

Safety outcomes include incidences of the following events within 2 years after randomization: (1) ISTH major bleeding; (2) ISTH major bleeding and clinically relevant non-major bleeding; (3) intracranial hemorrhage.

### Sample size estimates

2.6

The sample size was calculated based on the primary hypothesis and the results of our previous study. A retrospective study of 277 patients with NVAF and atherothrombotic disease demonstrated that the combination therapy group had a higher incidence of ischemic cardiovascular events and major bleeding than the OAC monotherapy group (33% vs. 19%/2 years, log-rank *p* = 0.04; unpublished data). Based on this result, we calculated that a maximum total sample size of 370 (equally-sized groups and the maximum number of events is 74) would be required to provide a power of 90% to detect a risk reduction in outcome events within 2 years, assuming lower event rates of 13 and 27% for each group, respectively, at an overall significance level of 2.5% with one-sided log-rank tests at an interim analysis and a final analysis (EAST® version 6.4, Cytel, Boston, MA, United States). An interim analysis was planned to assess the efficacy and futility when half the required number of events was observed. The critical values for the analyses were determined based on the Lan-DeMets error-spending method using an O’Brien-Fleming-type function with a non-binding boundary for futility. With a proposed 10% dropout rate, 400 participants will be recruited for this study.

### Statistical analyses

2.7

Analyses will be performed based on the intention-to-treat (ITT) principle. The data will be summarized using descriptive statistics. For the primary endpoint, survival curves will be estimated using the Kaplan–Meier method and compared between the two groups using the log-rank test. Hazard ratios with 95% confidence intervals will be calculated using a proportional hazards model. A per-protocol analysis will be performed to support the conclusions derived from the ITT-based analysis. Additionally, homogeneity of the treatment effects will be exploratively evaluated with the following subgroups: age (<80 vs. ≥80), sex, anticoagulant drug (warfarin vs. direct OACs), CHADS2 score (≤3 vs. 4 vs. ≥ 5), body weight (<60 kg vs. ≥60 kg), creatinine clearance (<30 mL/min vs. 30 ~ 50 mL/min vs. ≥50 mL/min), history of ischemic stroke and major bleeding, and prevalence of carotid or intracranial artery stenosis, hypertension, diabetes mellitus, dyslipidemia, and congestive heart failure.

Secondary endpoints will be analyzed in the same manner as the primary endpoints, except for the calculation of *p* values. Safety data will be analyzed descriptively for the treated set, which consists of all randomized patients who received at least one study treatment. The detailed plan for the interim and final analyses will be prespecified in the statistical analysis plan and finalized before the database lock. All statistical analyses will be conducted at the data center in the National Cerebral and Cardiovascular Center.

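### Kaplan–Meier is fixed for endpoints that leave out non-cardiovascular death; two-year incidences read from those curves would be slightly too high if such deaths are censored

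*Protocol article*

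**What the plan says.** Section 2.7 (Statistical analyses) fixes three tools for the primary endpoint. On curves: "For the primary endpoint, survival curves will be estimated using the Kaplan–Meier method", with a log-rank test to compare the arms. On the effect measure: "Hazard ratios with 95% confidence intervals will be calculated using a proportional hazards model". The approach then extends beyond the primary: "Secondary endpoints will be analyzed in the same manner as the primary endpoints", with p values left out.

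Section 2.5 (Study outcomes) defines the primary outcome as "a composite of ischemic cardiovascular events, including cardiovascular death, ischemic stroke, myocardial infarction, systemic embolism", plus ischemic events that need urgent revascularization, plus "significant bleeding, as defined by the International Society of Thrombosis and Hemostasis (ISTH) criteria". Deaths from other causes are not a component. Secondary outcomes (2), (3) and (5) also count only cardiovascular death. Outcome (4), ischemic stroke, names no death at all. Outcome (1) is death from any cause. The section describes the secondary outcomes as incidences over the two years from randomization.

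The article does not say how a non-cardiovascular death enters the curves, and it names no cumulative incidence function. Section 2.7 leaves the detailed plan to a statistical analysis plan that is not shown.

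**The concern.** A patient who dies of a non-cardiovascular cause without an earlier qualifying event can no longer have one. A standard Kaplan–Meier curve has only two outcomes, event or censored, so it censors this patient and in effect assumes the same future risk as in patients still alive. One minus the curve then estimates risk in a setting where nobody dies of other causes. It does not estimate the two-year incidence that section 2.5 describes.

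This matters for absolute figures. The article presents the trial as an assessment of net clinical benefit, and readers will probably take two-year risks and their difference from the curves. The population also makes competing deaths plausible: section 2.2 admits modified Rankin scores up to 4, and section 2.7 plans a subgroup aged 80 or over. For ischemic stroke alone, every death not itself counted as a stroke competes.

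**Working it through.** **1. The plan's own figures.** Section 2.6 assumes two-year event rates of 13% (monotherapy) and 27% (combination), with at most 74 events in 370 patients.
- Hazard ratio under constant hazards: ln(0.87)/ln(0.73) = 0.4425.
- Expected events: 370 × (0.13 + 0.27)/2 = 74, as stated.
- Freedman's formula, 90% power, one-sided 2.5%: 70.3 events for a fixed design. Taking an O'Brien-Fleming-type futility boundary (an assumption), the inflation for one interim look is 1.025, giving 72.1 events and 72.1/0.20 = 361 patients. Both are within 3% of the stated figures.

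The required number of events follows from the hazard ratio, alpha and power. The choice of curve estimator does not enter it.

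**2. Inputs for the comparison.**
- 13% and 27% from section 2.6, taken as what one minus Kaplan–Meier would show at two years.
- Two-year non-cardiovascular mortality x: not in the documents. Assumed 2 to 10%, equal in both arms.
- Constant cause-specific hazards (assumption).

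**3. Formulas.** For an arm with Kaplan–Meier risk p:
- event hazard h = −ln(1 − p)/2; competing hazard g = −ln(1 − x)/2;
- one minus Kaplan–Meier at two years = 1 − exp(−2h) = p;
- cumulative incidence at two years = h/(h + g) × [1 − exp(−2(h + g))].

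Example, p = 27%, x = 10%: 2h = 0.3147, 2g = 0.1054, so h/(h + g) = 0.7492. The bracket is 1 − 0.73 × 0.90 = 0.343. The product is 25.70%, an excess of 1.30 points.

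**4. Results.**

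| Assumed x | Incidence where KM shows 13% | Excess (points) | Incidence where KM shows 27% | Excess (points) | Risk difference (KM: 14.0) |
|---|---|---|---|---|---|
| 2% | 12.87% | 0.13 | 26.74% | 0.26 | 13.9 |
| 4% | 12.74% | 0.26 | 26.48% | 0.52 | 13.7 |
| 6% | 12.62% | 0.38 | 26.22% | 0.78 | 13.6 |
| 10% | 12.35% | 0.65 | 25.70% | 1.30 | 13.3 |

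The relative excess runs from about 1% to 5%. The risk ratio stays at 2.08 throughout.

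**5. Unequal mortality.** Combining rows of the table:
- 10% in the combination arm and 2% in the monotherapy arm: 25.70 − 12.87 = 12.8 points, so Kaplan–Meier overstates the difference.
- The reverse: 26.74 − 12.35 = 14.4 points, so Kaplan–Meier understates it.

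**6. Scale.** With 200 patients per arm, the standard error of one arm's risk is √(0.13 × 0.87/200) = 2.4 points and √(0.27 × 0.73/200) = 3.1 points. For the difference it is √(2.38² + 3.14²) = 3.9 points.

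**The case against.** The strongest reply has four parts.

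- **The censoring rule is inferred.** The article states none and leaves detail to an unseen analysis plan. This stands against saying flatly that the risks will be overstated; the point has to be conditional. It does not remove the point, because the estimator itself is named, and censoring is what that estimator does with a death that is not an event.
- **No two-year risk or risk difference is a planned effect measure.** The only one named is the hazard ratio. That is correct, and it limits the point to the curves and to any absolute risks reported from them. Even so, section 2.5 words the secondary outcomes as incidences.
- **The size is small and rests on an assumption.** This stands. Section 2.2 excludes active cancer, expected survival under two years, severe liver dysfunction and severe renal failure, which favors the lower part of any mortality range. Even at 15%, which nothing in the document supports, the same formula gives 25.0% and 12.0%, a difference of 13.0 points.
- **Some deaths are already covered.** A patient who dies after a qualifying major bleed has already had a primary event. This stands for the primary composite, but not for secondary outcomes without bleeding.

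A reader might also infer that the error must be larger for ischemic stroke alone because all deaths compete. The documents give no stroke rate to show this. With an assumed 5% two-year stroke risk and 10% competing mortality, the incidence is 4.75%: a relative excess of about 5% but only 0.25 points. The relative error can grow as more deaths compete, yet the absolute error can be smaller than for the composite.

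**Conclusion.** The point holds as a minor one. If non-cardiovascular deaths are censored, absolute two-year incidences read from the curves will be somewhat too high, by about 1.3 points at most under the assumed 2 to 10% mortality and constant hazards. That is well below one arm's standard error, but unlike sampling error it has a fixed direction within each arm, does not shrink with sample size and is avoidable.

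Two stronger readings are tempting and not supported. One is that the trial's main comparison is biased: the log-rank test and the Cox hazard ratio remain valid cause-specific comparisons, and the event target and all-cause mortality are untouched. The other is that the risk difference is always inflated: that follows for the planned rates when competing mortality is equal by arm, but can reverse when it is not.

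**What to change.** In section 2.7 and in the analysis plan:
- State how non-cardiovascular death is handled for each endpoint.
- Use Aalen-Johansen cumulative incidence for the curves, and for any reported two-year risks or differences, of endpoints with a competing death. The competing event is non-cardiovascular death for the primary and for secondary outcomes (2), (3) and (5), and any death not counted as the event for ischemic stroke.
- Keep the log-rank test and the Cox model, labeled as cause-specific analyses, and keep Kaplan–Meier for all-cause mortality.
- Report non-cardiovascular deaths by arm, so that a reader can judge the direction of any remaining difference.

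The cost is a few lines of wording and standard software, with no change to data collection, test, event target or sample size. The downside is one more curve definition to explain.

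### The primary log-rank test is stated without strata although allocation is minimized on three factors: a mildly conservative choice that is cheap to improve, with ischemic heart disease also missing from the subgroup list

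*Protocol article*

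**What the plan says.** Section 2.3 (Randomization) of the protocol article assigns patients 1:1 "using the Pocock-Simon minimization method, with adjustment for sex, history of ischemic heart disease, and history of acute ischemic stroke".

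Section 2.7 (Statistical analyses) has the Kaplan-Meier curves for the primary endpoint "compared between the two groups using the log-rank test", and adds that "Hazard ratios with 95% confidence intervals will be calculated using a proportional hazards model". It names no stratification factor for the test and no covariate for the model, and it excludes none. It then leaves the detail to another document: "The detailed plan for the interim and final analyses will be prespecified in the statistical analysis plan and finalized before the database lock".

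Section 2.6 (Sample size estimates) sizes the trial "at an overall significance level of 2.5% with one-sided log-rank tests at an interim analysis and a final analysis", again without strata. It gives 370 patients and 74 events for 90% power.

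Section 2.7 also lists the exploratory subgroups. Sex and history of ischemic stroke are on the list, as are carotid or intracranial stenosis and several comorbidities. History of ischemic heart disease is not.

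**The concern.** Minimization removes most of the chance imbalance between arms in the chosen factors. The variance of an analysis that ignores those factors still allows for that imbalance. If the factors predict outcome, the standard error is therefore somewhat too large for the design: the test rejects less often than its nominal level under the null, and a little power is lost. The three factors are plausible predictors of a composite that contains ischemic stroke, myocardial infarction and cardiovascular death.

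The subgroup gap matters for interpretation. The Introduction cites two randomized trials of anticoagulant monotherapy, both in patients with atrial fibrillation and stable coronary disease. Table 1 of this trial admits patients with or without heart disease. Whether the result is similar in the two groups is an obvious exploratory question, and the list does not ask it.

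**Working it through.** **1. The plan's own figure.** Section 2.6 assumes 2-year event rates of 13% and 27%.
- Hazard ratio: ln(0.87)/ln(0.73) = 0.4425.
- Freedman events, one-sided 2.5%, 90% power: (1.960 + 1.282)² × [(1 + 0.4425)/(1 − 0.4425)]² ≈ 71.
- Two looks with O'Brien-Fleming-type spending and an assumed futility bound of the same type inflate this by about 1.026: 71 × 1.026 ≈ 73 events.
- Mean event rate (13% + 27%)/2 = 20%, so 73/0.20 = 365 patients.

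The stated 370 patients and 74 events (370 × 0.20) are reproduced to within about 2%, using log-rank theory without strata.

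**2. Unstratified against stratified log-rank at the planned effect.** The documents give neither prevalence nor prognostic strength for the factors, so both are assumed. Settings: 370 patients, minimization with a 0.8 biased coin, prevalences 40/35/40%, the same hazard ratio for each factor, event rates 27% and 13%, 6,000 trials per row, one look at z = 1.96, no dropout. The stratified test uses all 2 × 2 × 2 = 8 cells.

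| Factor HR | Error, unstratified | Error, stratified | SD of null z, unstratified | Power, unstratified | Power, stratified |
|---|---|---|---|---|---|
| 1.0 | 0.026 | 0.028 | 1.01 | 93.1% | 92.8% |
| 1.3 | 0.022 | 0.024 | 1.00 | 93.3% | 92.8% |
| 1.5 | 0.022 | 0.023 | 0.99 | 93.4% | 93.6% |
| 2.0 | 0.018 | 0.021 | 0.95 | 94.0% | 94.5% |
| 3.0 | 0.014 | 0.025 | 0.91 | 94.1% | 96.5% |

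The Monte Carlo standard error of the error rates is √(0.025 × 0.975/6000) ≈ 0.002. The SD column gives a smoother check, because the error is about Φ(−1.96/SD). With SDs of 0.987, 0.953 and 0.906 this is 0.0235 at a factor HR of 1.5, 0.020 at 2.0 and 0.015 at 3.0. The conservatism is real and grows with factor strength, but at 1.5 it is slight.

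**3. Unadjusted against covariate-adjusted Cox.** Settings: 400 patients, 10% dropout, prevalences 35/40/50%, 0.8 biased coin, one look, 2,500 trials per row. The weaker treatment effect is the one implied by the retrospective study in section 2.6: ln(0.81)/ln(0.67) = 0.526.

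| Treatment HR | Factor HRs | Unadjusted | Adjusted | Gain (points) |
|---|---|---|---|---|
| 0.4425 (planned) | 1.3/2/2 | 92.9% | 93.8% | 0.9 |
| 0.4425 (planned) | 1.2/1.6/1.5 | 93.0% | 93.3% | 0.3 |
| 0.526 | 1.3/2/2 | 79.8% | 81.8% | 2.0 |
| 0.526 | 1.2/1.6/1.5 | 79.2% | 80.5% | 1.3 |

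Each power figure has a standard error of about 0.5 to 0.8 points, so only the direction and rough size should be read. A separate set of 5,000 trials per scenario at a treatment HR of 0.53 gave 79.4% against 81.6%, and 78.4% against 79.2%. With factor HRs of 1.3/2/2 the one-sided error was 0.0206 unadjusted and 0.0238 adjusted. In 8,000 trials at that treatment HR, the eight-stratum log-rank moved power from 79.4% to 80.8% with the stronger factors and from 79.9% to 79.8% with the weaker ones.

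**4. Effect on the estimate.** At a true HR of 0.526 with factor HRs of 1.3/2/2, the mean estimate was 0.530 unadjusted and 0.519 adjusted, a small difference.

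**5. Does leaving out the interim look matter?** With 74 events, calculated power is 93.9% for one look, 93.8% for two looks, and 93.0% with the assumed futility bound. It does not change the reading.

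**The case against.** The strongest objection is that the article is silent rather than wrong. It defers the detailed plan to a statistical analysis plan that is not shown, and strata and Cox covariates are details that such a plan usually holds. This stands in part. A reader might infer that the plan commits to an unadjusted Cox model. It does not: covariates are neither named nor ruled out. What remains is that the log-rank test is named in two sections, once as the basis of the sample size and boundaries, each time without strata.

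Other stronger readings also fail.
- *The test is invalid.* The departure is in the conservative direction, and only if the factors are prognostic.
- *The trial is underpowered for this reason.* Power near 79% comes from a treatment HR of about 0.53, not the planned 0.44. With a 27% control rate, that HR means about 15% in the other arm (1 − 0.73^0.526 = 0.153) instead of 13%. At the planned effect, power is about 93% either way.
- *The unadjusted hazard ratio is biased.* It estimates a marginal effect and the adjusted one a conditional effect. Choosing between them is a choice of what to estimate.
- *The trial cannot inform on patients without coronary disease.* The factor is recorded at randomization, so the analysis remains possible. It is simply not listed, and with about 74 events it would be imprecise.

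The remedy also has a price: an adjusted Cox test is not the test used for sizing. This is fair, and the fix below allows for it.

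**Conclusion.** The point holds as a modest improvement in efficiency and alignment. The primary test as written does not use the factors that constrain allocation. For assumed factor HRs of 1.5 to 2, the simulated one-sided error is about 0.018 to 0.022, and the power given up is about 0 to 2 points. The upper end applies to covariate adjustment under a treatment effect weaker than planned. An eight-cell stratified log-rank recovers little or nothing unless the factors are strong. With factor HRs of 1.3 or less there is no power to recover by stratifying. These sizes rest on assumed prevalences, factor strengths and biased-coin probability, none of which the documents give. Neither validity nor the planned 90% power is threatened.

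The subgroup omission rests on explicit text: two of the three minimization factors are on the list and ischemic heart disease is not.

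**What to change.** - State in the statistical analysis plan, before database lock, that the primary hazard ratio, 95% confidence interval and test come from a Cox model adjusted for sex, history of ischemic heart disease and history of ischemic stroke, as recorded at randomization. With about 74 events this is preferable to eight strata, which average 74/8 ≈ 9 events each.
- Apply the group-sequential boundaries to that same test. The choice therefore has to be fixed before the interim look if that is still to come.
- Keep the unadjusted log-rank test as a sensitivity analysis. It preserves the link to the sample size calculation.
- Describe the adjusted hazard ratio as a conditional effect.
- Add history of ischemic heart disease (yes/no) to the exploratory subgroups in section 2.7.

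The cost is wording in the analysis plan and protocol. No new data are needed. The small downsides are the conditional interpretation and a primary test that differs from the one used for sizing.
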